### Description of the surgical procedures

#### Conventional full median sternotomy

The patient is positioned supine (dorsal decubitus). The skin is incised from the suprasternal notch to the xiphoid process. Conventional median sternotomy is performed from the manubrium to the xiphoid. The ascending aorta and right atrium are cannulated centrally to initiate CPB. A vent cannula for the left-sided cavities is placed in the right superior pulmonary vein, followed by aortic cross-clamping. Intermittent cold antegrade blood cardioplegia via the root or coronary ostia every 20 min, transverse aortotomy, valve extraction and decalcification of the annulus are performed. AVR is performed using Ti-Cron 2/0® polyester suture stitches supported by Teflon in an aortic ring. The aortotomy is closed using polypropylene monofilament 4/0, followed by aortic unclamping, decannulation and placement of a transitional pacemaker placement. Placement of two sub -xiphoid Blake type drains. Sternal closure with stainless steel wires. The skin incision is closed with a subcutaneous double layer and staples or intradermic suture.

#### Ministernotomy

The patient is positioned supine (dorsal decubitus) and defibrillator external paddles are positioned. An 8 to 10-cm opening is made in the skin starting at the sternal angle. Ministernotomy is defined as a partial upper hemisternotomy extended into a J-shape into the right fourth intercostal space irrespective of the skin incision (usually 8–12 cm in length, Fig. 1). A 21-mm silicon Blake-type drain is inserted sub-xiphoid. CO2 is administered via the sub-xiphoid drain placed before the CPB was established. The rest of the procedure is similar to that used for FS.

### Independent variables in the study. Complications

Data on preoperative baseline demographic variables will be recorded in both intervention groups. Most of the definitions of postoperative complications are to be found in the consensus document, *Valve Academic Research Consortium 2* (VARC2) [30] that arose as a consequence of the generalisation of TAVI, and the need for consistency of definitions and improved comparability of articles. The AKIN classification was used in the VARC 2 criteria according to the European Society of Cardiology (ESC)/European Association for Cardio-Thoracic Surgery (EACTS) recommendations, and it is the only way to compare new data with previous reports/trials of TAVI [30].

### Statistical analysis

Statistical analysis will be performed using IBM SPSS 22.0® for Windows®. First, a descriptive analysis of the study variables will be conducted; the values of quantitative variables will be expressed as mean ± standard deviation (SD) or median (interquartile range) depending on whether distribution of the variable is symmetrical and normal. Qualitative variables will be presented in absolute frequencies and relative frequencies. To analyse the differences between continuous quantitative variables (values of the EQ-5D-5 L® and SATISCORE questionnaires) in the two independent groups (MS vs. FS), Student’s *t* test for two independent samples will be applied in cases where the normality of distribution of the variable data in each of the groups can be accepted, which will be checked using the Kolmogorov-Smirnov test, then histograms and Q-Q plots. In cases where normality cannot be accepted, the corresponding non-parametric Wilcoxon test will be applied. In cases where the normality condition can be accepted, Student’s *t* test for two-tailed samples will be applied to analyse differences between continuous quantitative variables in two associated groups (QOL data) before and after surgery.

We will apply analysis of variance (ANOVA) for repeated measures to analyse the variability, with repeated measurements over time, of certain continuous quantitative determinations of the questionnaires used. The normality of the remainder will be checked using the Shapiro-Wilk test. In the case of statistically significant differences in the contrasted variables measured at different times, the different levels of time will be checked, adjusting the outcomes using the Bonferroni correction.

To analyse if there are differences between qualitative variables, 2 × 2 tables will be prepared and analysed using the Chi-squared (*X*2) statistical test. This analysis will be performed to evaluate the differences in complications and major adverse events of dichotomous variables. The relative risk ratio and the corresponding confidence intervals will be calculated to 95% for the MS versus FS technique as a combined safety endpoint of MAC complications.

Multivariate regression analysis techniques will be applied to control possible bias in effect caused by the patient’s initial situation (comorbidities). Pearson’s correlation test will be performed on EQ-5D-5 L® and SATISCORE® data. Survival analysis will be conducted using Mantel Cox log-rank analysis with the corresponding Kaplan-Meier survival chart.

The “intention to treat” population is defined to include all randomised subjects. This population will be used for endpoint analyses. The as-treated population (“per protocol”) is defined to include all subjects undergoing the index procedure. This population will be used for the analysis of adverse events.

Differences between MS and FS group scores at each follow-up time point will be estimated with longitudinal random-effect growth curve models, which will be fit to the repeated measurements for each health status outcome. These longitudinal analyses will use all available quality-of-life data: including data from patients who will subsequently die, withdraw, or will be lost to follow up. They will also accommodate missing data under the missing at random assumption. Variables that will be included in the models are: treatment assignment, pre-specified patient characteristics (age, sex, EuroScore), follow-up time and interactions between treatment and time. These models will be used to calculate the mean between-group differences in the EQ-5D index score and the individual subscales at each follow-up time point, and the associated 95% CIs and *P* values.

To examine the potential impact of missing data, which, given the illness severity of the trial population, would most likely not be missing at random, we will repeat the growth curve analyses after imputing the missing scores among the surviving patients, as the lowest reported score among respondents within each treatment group for each respective time point. We also will examine the magnitude of potential survivor bias by comparing the mean baseline scores between treatment groups for the subgroups of patients with available QOL data at each successive follow-up time point.

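### The repeated-measures ANOVA would usually drop the early scores of patients who miss a later visit, at odds with the plan's all-randomised, all-available-data rules; the effect is confined to the ANOVA's own results (minor)

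*Protocol article*

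**What the plan says.** All of this is in the protocol article under Statistical analysis, unless another section is named.

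- **ANOVA.** "We will apply analysis of variance (ANOVA) for repeated measures to analyse the variability, with repeated measurements over time". It applies to some of the questionnaire scores, which are not listed.
- **Follow-up step.** "In the case of statistically significant differences in the contrasted variables measured at different times, the different levels of time will be checked", with a Bonferroni adjustment.
- **Software.** SPSS 22.0 is named, but not the procedure. No rule for missing visits is attached to the ANOVA.
- **Population.** The intention-to-treat "population is defined to include all randomised subjects. This population will be used for endpoint analyses".
- **Arm comparison.** Differences between ministernotomy and full sternotomy at each follow-up time are assigned to random-effect growth curve models with a treatment-by-time interaction, reported with 95% CIs and P values. These models use every available quality-of-life score, including scores from patients who later die, withdraw or are lost, and they assume missing at random.
- **Missing data.** The authors expect that missing scores "would most likely not be missing at random". They therefore repeat the growth curve analysis with lowest-score imputation among survivors and add a survivor-bias check.
- **Visits.** EQ-5D-5L is completed at baseline, 1, 6 and 12 months, and SATISCORE at 1 and 6 months (Quality of life and satisfaction questionnaires).

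**The concern.** Classical repeated-measures ANOVA needs a full set of visits from each patient. A patient who completes baseline and 1 month and then dies or withdraws contributes nothing, although two scores were observed. In general such an analysis is safe only if data are missing completely at random. That is a stronger condition than the missing-at-random assumption of the growth curve models, and the plan itself doubts even the weaker one.

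One section therefore holds two analyses of the same scores that differ in who is analysed and in what is assumed about the missing data. The imputation analysis and the survivor-bias check are built around the growth curve models, and nothing comparable is attached to the ANOVA. If patients who are doing badly leave, its completers look better early than the randomised patients did. That distorts the estimated recovery over time. If the loss also differs by arm, it distorts any arm effect read from the same table.

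**Working it through.** **1. The plan's own figure.** Inputs from Sample size calculation: difference 0.10, SD 0.15, two-sided alpha 0.05, power 90%. n per arm = 2 × (1.960 + 1.282)² × 0.15² / 0.10² = 47.3, so 48 per arm and 96 in total, as stated. Power at 48 per arm is 90.4% by the normal approximation and 89.8% by the t distribution.

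**2. Assumptions for the bias.** The documents give no dropout rate and no correlation between visits. Assumed: 50 per arm, normal scores with SD 0.15 at every visit, correlation 0.5 between any two visits, no true arm effect. Patients in the lowest 10% at 1 month leave after that visit, and the ANOVA drops all their scores.

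**3. Shift in the completers' means.** Removing the lowest 10% of a standard normal raises its mean by φ(−1.282)/0.90 = 0.1755/0.90 = 0.195.

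- 1-month mean: 0.195 × 0.15 = 0.029.
- Baseline, 6-month and 12-month means: 0.5 × 0.029 = 0.0146.
- Mean of the three follow-up visits: (0.029 + 0.0146 + 0.0146)/3 = 0.0195.

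**4. Change over time, same loss in both arms.** The 1-month change from baseline is overstated by 0.029 − 0.0146 = 0.0146. Simulation gives 0.014 to 0.015, depending on whether the cut is a fixed threshold or exactly the lowest five of 50. The 1-to-6-month change is biased by the same amount in the other direction. With equal correlations the baseline-to-6-month and baseline-to-12-month changes are not shifted, so in this scenario the distortion lies in the contrasts that involve 1 month.

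**5. Arm difference, same loss in both arms.** The shifts cancel and the bias is zero.

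**6. Arm difference, loss in one arm only (extreme).** 45 and 50 patients remain, and √(1/50 + 1/45) = 0.2055.

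| Quantity tested | Bias | SD | Standard error | Bias/SE | Two-sided 5% test rejects |
|---|---|---|---|---|---|
| Raw score averaged over three visits | 0.0195 | 0.15 × √(2/3) = 0.1225 | 0.0252 | 0.77 | 12.1% |
| 1-month change from baseline | 0.0146 | 0.15 × √(2 × 0.5) = 0.15 | 0.0308 | 0.47 | 7.6% |

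Simulation gives 12 to 13% and about 7.5%. The raw 1-month difference is biased by 0.029.

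**7. Milder patterns.** In a separate simulation, dropout depended on the 1-month score in the same way in both arms but at different rates (intercepts of 2% against 10%, or 5% against 20%; correlation 0.3 to 0.7). The complete-case arm difference was 0.006 to 0.015, with 5.1 to 8.6% false positives. An estimate valid under missing at random, standing in for the growth curve model, stayed within 0.002 of zero in every setting.

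**8. Numbers retained.** Without replacement, assumed losses of 10%, 15% and 20% leave 45, 42 and 40 per arm, with power of 88.5%, 86.3% and 84.6% (normal approximation).

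**The case against.** The strongest reply is that the ANOVA is not the arm comparison. Its stated purpose is variability over time, and its Bonferroni step compares times; for that purpose, opening the step on a time difference is coherent. The arm differences belong to the growth curve models, which keep the very scores at issue. A reader might infer that the trial's main result rests on completers, or that the ANOVA's P values will decide the trial because it carries the only stated multiplicity correction. The text does not support either inference: it assigns the arm-difference P values to the growth curve models. This stands, and it limits the point to the ANOVA's own output.

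The document also never says that only complete cases are kept. That is a property of the usual procedure, and the procedure is not named. This stands as a caution. However, the all-available-data rule is written for the growth curve models, and no rule changes the ANOVA's usual behaviour.

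A false arm difference is tempting to claim outright. It needs score-related loss that differs between arms, and nothing in the document shows that this will occur. On change from baseline, the scale of the primary endpoint, even the extreme case gives about 7.5% at 1 month and close to 5% at later visits.

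Nor does it follow that the trial falls below 96 patients. Sample size calculation continues recruitment to that minimum and considers an extra patient for each one without the 1-year assessment, and questionnaires may be completed by telephone. Replacement restores numbers but not the dropped scores, so the power loss is a side issue.

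Finally, the growth curve model is not immune. It stays near zero in the check because the simulated loss depends on an observed score. Loss that depends on unobserved scores could bias it too.

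**Conclusion.** The point holds in a limited form and is minor. As usually run, the ANOVA conflicts with the section's own analysis population, its all-available-data approach and its expectation of informative missingness. Its time contrasts can be biased even when both arms lose patients alike: about 0.014 on the 1-month change from baseline under the assumptions above, roughly one seventh of the 0.10 target. An arm effect taken from it is unbiased with equal loss. With score-related loss of 10% in one arm only, it is biased by 0.029 at 1 month, with about 12 to 13% false positives on raw scores averaged over visits and about 7.5% on 1-month change. The size depends on assumed dropout and correlation, for which the document gives no figures, and on the ANOVA being run in its usual complete-case form.

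**What to change.** Take the time contrasts and the arm-by-visit test, with the Bonferroni correction, from the longitudinal mixed model already planned, using all available scores of all randomised patients. Delete the repeated-measures ANOVA, or keep it labelled as a complete-case sensitivity analysis. Because the mixed model assumes missing at random, the planned lowest-score imputation analysis should stay.

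The cost is a sentence or two under Statistical analysis. No new data, visits or patients are needed, and the sample size does not change.

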### Selection of patients, randomisation and follow up

The study will recruit patients over the age of 18 years, who have severe aortic stenosis or double aortic lesion with predominant stenosis, who are symptomatic according to current guidelines [26] and also meet the inclusion and exclusion criteria (Table 2). All patients will receive oral and written information from a staff surgeon about the study and then as an informed patient sign a consent form before their inclusion and randomisation in the study. These data were recorded in the hospital computerized healthcare database.

**Table 2 Tab2:** Inclusion and exclusion criteria

Inclusion criteria
• Severe aortic stenosis (calcified aortic valve, aortic valve area < 1 cm^2^ or body surface area index < 0.6 cm^2^, mean transvalvular gradient > 40 mmHg or peak systolic velocity > 4 m/s) or double aortic lesion with predominance of stenosis
• Sympotomatic (dyspnea NYHA score ≥ 2, angina or syncope)
• Age ≥ 18 years
• Capacity to give informed consent
Exclusion criteria
• Moderately depressed ejection fraction (< 40%)
• Prior heart surgery (redo operation)
• Emergent surgery (within the first 24 h of admission)
• Infectious endocarditis
• Chronic obstructive pulmonary disease greater than moderate (forced expiratory volume at 1 s (FEV1) predicted < 60% measured by spirometry)
• Need for concomitant surgery except Morrow myectomy preoperative or intraoperative

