### Study endpoints

The primary endpoint measure is to detect differences between MS (active treatment) and FS (control) greater than or equal to 0.10-point change from the baseline questionnaire EQ-5D-5 L® Index, at 1, 6 or 12 months after the surgery.

The secondary endpoint measures are:Differences between intervention groups greater than or equal to 10 point-change from the baseline questionnaire EQ-5D-5 L® utilities such as VAS, SI and HI at 1, 6 or 12 months post-surgery.Early postoperative combined endpoint of four major adverse complications (MAC) at 1 month (safety endpoint), including all-cause mortality, acute myocardial infarction, stroke or transient ischaemic accident, and classification of acute renal failure by Acute Kidney Injury Network (AKIN) greater than or equal to 2. Follow up at 1 year post-surgery.Severe nosocomial infections (pneumonia, early endocarditis, mediastinitis, sepsis).Need for rehospitalisation.Differences between interventions groups greater than or equal to 10 points change from the baseline SATISCORE® questionnaire at 1 and 6 months post-surgery.Postoperative hospital length of stay.Postoperative intensive care unit length of stay.Times for ischaemia and cardiopulmonary bypass (CPB).Mechanical ventilator support after surgery (intubation times).Bleeding in the first 24 h after surgery and transfusion requirements in the first 72 h.New York Heart Association (NYHA) functional class at 1 to 6–12 months.Survival at 12 months.

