### Sample size calculation

A review of previous work [28, 29] shows that the standard deviations of the EQ-5D-5 L® index in cardiovascular disease varies between 0.10 and 0.22, while VAS score varies between 8 and 21 depending on the severity. Likewise, in the only (multicentre) study [17] that determines quality of life in aortic stenosis, the standard deviation for high-risk patients scheduled for AVR was 0.17 in patients randomised to FS versus TAVI. For these reasons, on summary of all previous work, we used a standard deviation of 0.15 for the EQ-5D-5 L® index to calculate the sample size.

In QOL studies, it is not only important to ascertain whether there are significant differences, but also to know if these differences are clinically relevant. This is why the concept of the **minimal important difference (MID)** was created, which in previous research among patients with cancer was 0.08 points on the EQ-5D index and 7–11 points on the VAS [29], and in patients with stroke it was 0.10 points on the EQ-index (95% CI 0.08–0.12) [28]. This difference was also 0.06 points (95% CI 0.02–0.10) on the EQ index during the first month in the PARTNER 1 study (transfemoral TAVI versus FS) [17], and 0.12 (95% CI 0.08–0.16) in the CoreValve PIVOTAL trial study [18]. As there was no existing specific calculation of MID for cardiology patients with severe aortic stenosis, we arbitrarily established the interval of 0.10 points on the EQ-5D index (the mean value from previous studies) as the clinically relevant difference to detect. Thus, to detect an MID of at least 0.10 points in the QOL scale EQ-5D-5 L® index, with alpha error of 0.05, beta error of 0.1 and power of 90% for two-tailed contrast of two independent means (SD 0.15), two groups of 48 patients are necessary to provide a minimum of 96 patients. In view of possible losses to follow up, 100 patients will be randomised. If patients drop out or are excluded during the study, additional patients will be recruited until a minimum of 96 patients is achieved, and inclusion of an additional patient will be considered again for each patient not completing the 1-year follow-up assessment.

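### The only between-group rule stated for qualitative variables is a 2 × 2 chi-squared test, which does not fit ordinal NYHA class and leaves either its cut or its test open

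*Protocol article*

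**What the plan says.** Under Study endpoints, the protocol article lists "New York Heart Association (NYHA) functional class at 1 to 6–12 months" among the secondary endpoints, with no cut-point. Table 2 uses the same scale as a graded score for eligibility: "dyspnea NYHA score ≥ 2, angina or syncope".

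Under Statistical analysis, the rule for categorical data opens: "To analyse if there are differences between qualitative variables, 2 × 2 tables will be prepared and analysed using the Chi-squared" test. The sentence after it reads: "This analysis will be performed to evaluate the differences in complications and major adverse events of dichotomous variables".

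The other methods in that section are written for other data:

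- The t test is for the EQ-5D-5L and SATISCORE values, treated as continuous. Its fallback belongs to the same rule: "In cases where normality cannot be accepted, the corresponding non-parametric Wilcoxon test will be applied".
- Repeated-measures ANOVA is for continuous questionnaire measurements.
- The growth curve models, "which will be fit to the repeated measurements for each health status outcome", are described as using quality-of-life data and yield mean differences in the EQ-5D index and subscales.

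NYHA is not named anywhere in the statistical section.

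**The concern.** With two arms, a 2 × 2 table has room for two outcome categories. NYHA class conventionally has four ordered levels (the article does not list them), so it can enter such a table only after classes are merged. Merging counts a move within the merged classes as no change. If class III–IV is uncommon after valve replacement, a cut there also gives small expected counts.

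Because no cut is stated, someone would have to choose one, possibly after seeing how patients are distributed. A real difference in functional class could then be missed, or a result could hold at one cut and not at another. NYHA is the functional outcome rated outside the questionnaires, so this is not fully covered elsewhere in the endpoint list.

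**Working it through.** **1. Which rule reaches NYHA?**

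- Reading A: the opening of the categorical rule covers all qualitative variables. NYHA then goes into a 2 × 2 table and must be collapsed at an unstated cut.
- Reading B: the following sentence restricts the rule to dichotomous complications and major adverse events. NYHA is neither, so it has no assigned test.

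The text allows both readings, and neither gives NYHA an ordinal analysis.

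**2. Sample size used for the check.** The Sample size calculation section gives a difference of 0.10, SD 0.15, two-sided alpha 0.05 and power 90%. The formula is n per arm = 2(z₀.₉₇₅ + z₀.₉₀)² × SD²/difference².

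n = 2 × (1.960 + 1.282)² × 0.15²/0.10² = 2 × 10.51 × 2.25 = 47.3, so 48 per arm and 96 in total. This reproduces the stated figure. It is for the EQ-5D index; no power is stated for NYHA.

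**3. Assumptions for NYHA (none are in the documents).** Four levels; the control-arm distributions shown below; and a common odds ratio (OR) that shifts the ministernotomy arm towards lower classes.

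The shift multiplies each cumulative odds by the OR. For controls at 50/40/9/1% and OR 2.5:

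- Class I: odds 0.50/0.50 = 1, becoming 2.5, so 2.5/3.5 = 71.4%.
- Class I–II: odds 0.90/0.10 = 9, becoming 22.5, so 22.5/23.5 = 95.7%. That leaves 4.3% in class III–IV.
- Expected count per III–IV cell: 48 × (0.100 + 0.043)/2 = 3.4, which is small for a chi-squared test.

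**4. Power by simulation.** 20,000 trials per setting, 48 per arm, two-sided 0.05. The tie-corrected Wilcoxon rank-sum test is compared with the uncorrected 2 × 2 chi-squared test at each of two cuts. Gains are in percentage points.

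| Control I/II/III/IV, % | OR | Rank test, % | I–II vs III–IV, % | Gain | I vs II–IV, % | Gain |
|---|---|---|---|---|---|---|
| 60/33/6/1 | 2.5 | 53.1 | 14.9 | 38.2 | 53.5 | −0.4 |
| 60/33/6/1 | 3 | 66.5 | 17.7 | 48.8 | 66.8 | −0.3 |
| 50/40/9/1 | 2.5 | 59.1 | 21.5 | 37.6 | 57.7 | 1.4 |
| 50/40/9/1 | 3 | 74.0 | 26.4 | 47.6 | 72.7 | 1.3 |
| 40/45/13/2 | 2.5 | 63.1 | 27.9 | 35.2 | 60.9 | 2.2 |
| 40/45/13/2 | 3 | 77.6 | 36.3 | 41.3 | 75.7 | 1.9 |
| 30/45/20/5 | 2.5 | 65.9 | 39.8 | 26.1 | 58.8 | 7.1 |
| 30/45/20/5 | 3 | 80.4 | 51.4 | 29.0 | 74.9 | 5.5 |
| 20/40/30/10 | 2.5 | 67.6 | 53.7 | 13.9 | 52.0 | 15.6 |
| 20/40/30/10 | 3 | 82.9 | 68.2 | 14.7 | 69.5 | 13.4 |
| 25/25/25/25 | 2.5 | 69.4 | 58.3 | 11.1 | 56.2 | 13.2 |
| 25/25/25/25 | 3 | 83.3 | 72.3 | 11.0 | 72.8 | 10.5 |

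**5. Checks.** With no true difference (OR 1), the rank test rejected in 4.9–5.2% of trials and the two chi-squared tests in 4.7–6.0%, so a lenient rank test does not explain the gains. The closed-form two-proportion power for the III–IV cut in the 50/40/9/1%, OR 2.5 setting is 18.9%, close to the simulated 21.5%. A rerun with 200,000 trials per setting agreed with the table to within about one point.

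**6. Reading the table.** When 7–25% of controls are in class III–IV, the gain over the III–IV cut runs from 26.1 to 48.8 points, and over the class-I cut from −0.4 to 7.1. When 40–50% are in class III–IV, both cuts lose about 10 to 16 points. For the same data (50/40/9/1%, OR 2.5), power is 21.5% at one cut and 57.7% at the other.

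**The case against.** The strongest reply is Reading B: the sentence after the rule names complications and dichotomous events, so the article may never have meant NYHA to go into a 2 × 2 table. What remains would then be an unnamed test for one secondary endpoint, which a condensed article may leave to the full protocol or analysis plan. This stands in part. A reader might infer that the plan requires NYHA to be dichotomised; the article does not say so. But the opening of the rule is unrestricted, it is the only between-group test stated for categorical data, and it is the wrong shape for this endpoint. That is a poorly fitting stated rule as well as an omission.

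A reader might also infer that the trial will lose more than half its power on NYHA. The documents do not support that either. The I–II versus III–IV cut appears nowhere in them, and if class III–IV is rare after surgery, the I versus II–IV cut loses almost nothing.

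Three further points stand. All the distributions and odds ratios are assumed. The simulation uses a common odds ratio across levels, which suits an ordinal test; an effect confined to one threshold could favour a cut placed there. And class frequencies will be tabulated in any case, so shifts between classes would still be visible descriptively.

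**Conclusion.** The point holds in limited form. The stated categorical rule does not fit NYHA class: depending on the reading, the endpoint is either collapsed at an unstated cut or left without a fitting test. With 48 per arm, odds ratios of 2.5 to 3 and at most about 25% of controls in class III–IV (all NYHA inputs assumed), an ordinal test gains about 26 to 49 points over one plausible cut and about 0 to 7 over the other. It was never materially worse in the settings tried; its largest deficit was 0.4 points. The main weakness is therefore that the result could turn on an unfixed choice of cut, rather than a certain loss of power. It affects one secondary endpoint for which the trial was not powered, and leaves the EQ-5D primary analysis untouched. It is worth correcting because the correction is so cheap.

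**What to change.** In the Statistical analysis section, limit the 2 × 2 chi-squared test to dichotomous outcomes. Add that NYHA class at each follow-up visit will be compared between arms on all its levels, by a Wilcoxon rank-sum test or by a proportional-odds model adjusted for baseline NYHA class where available. With the model, report a common odds ratio and its 95% CI. Tabulate the class percentages by arm beside it, and treat any dichotomy as secondary. If the investigators prefer a dichotomy, fixing and justifying the cut before the data are examined would at least remove the dependence on a later choice.

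The cost is one sentence. NYHA is already an endpoint, so no new data are needed; a Wilcoxon test is already in the plan for other variables, and ordinal regression is available in the named software. The downside is that a common odds ratio is less familiar to clinical readers than a percentage, which the tabulated percentages offset.

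### Two unranked analyses serve the between-arm EQ-5D comparison, and the growth model's stated covariates omit the baseline EQ-5D index

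*Protocol article*

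**What the plan says.** Under Study endpoints, the protocol article defines the primary endpoint as a between-arm difference of at least 0.10 in change from the baseline EQ-5D-5L index, at 1, 6 or 12 months. The baseline questionnaire is completed once consent is signed (Quality of life and satisfaction questionnaires).

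The Statistical analysis section then gives these procedures for EQ-5D:

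- A two-sample t test on the questionnaire values of the two arms. Normality is checked by Kolmogorov-Smirnov and then by plots. "In cases where normality cannot be accepted, the corresponding non-parametric Wilcoxon test will be applied".
- "We will apply analysis of variance (ANOVA) for repeated measures", introduced for the variation over time of certain questionnaire measures, with Bonferroni correction across time levels.
- A longitudinal model: differences between the arms' scores at each visit "will be estimated with longitudinal random-effect growth curve models". It yields mean differences, 95% CIs and P values at each visit. Its terms are "treatment assignment, pre-specified patient characteristics (age, sex, EuroScore), follow-up time and interactions between treatment and time".
- Multivariate regression to control for the patient's initial situation, which the text glosses as comorbidities.

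No procedure is called the primary analysis, and none lists the baseline EQ-5D index as a covariate.

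**The concern.** Two procedures answer the same between-arm question and can give different P values. One of them also branches on a data-dependent check. If neither is named in advance, the choice can be made after the results are seen.

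The variable to be analysed is not settled either. The endpoint is a change, while the t/Wilcoxon comparison and the growth model are worded for scores. A score comparison and a change comparison treat a chance baseline difference between the arms in opposite ways, so they are not interchangeable in a trial of about 100 patients.

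The article does publish a covariate list, and that list leaves out the baseline value of the outcome itself. This forgoes precision that would cost no extra data.

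**Working it through.** **Inputs.** From Sample size calculation: "we used a standard deviation of 0.15 for the EQ-5D-5 L® index to calculate the sample size"; the aim is "to detect an MID of at least 0.10 points in the QOL scale"; alpha 0.05 two-sided, power 90%; "two groups of 48 patients are necessary to provide a minimum of 96 patients". The correlation rho between baseline and follow-up index is not in the article. It is assumed here at 0.3, 0.5 and 0.7. The SD is taken as 0.15 at baseline and at follow-up.

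**Step 1: the plan's own figure.** n per arm = 2 × (1.960 + 1.282)² × 0.15² / 0.10² = 47.3, rounded up to 48, so 96 in total. The stated size is reproduced. Power at 48 per arm is 90.4% by the normal formula and 89.8% by the noncentral t. The t figures are used below.

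**Step 2: SD under each choice of analysed variable.**

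- Follow-up score, unadjusted: 0.15.
- Change score: 0.15 × √(2(1 − rho)).
- Baseline-adjusted: 0.15 × √(1 − rho²).

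The adjusted variance is therefore (1 − rho²) times that of the follow-up score and (1 + rho)/2 times that of the change score.

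**Step 3: results** (difference 0.10, 48 per arm, one visit).

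| rho (assumed) | SD, change | SD, adjusted | Variance ratio, adjusted to score | Variance ratio, adjusted to change | Power, score | Power, change | Power, adjusted |
|---|---|---|---|---|---|---|---|
| 0.3 | 0.1775 | 0.1431 | 0.91 | 0.65 | 89.8% | 78.0% | 92.3% |
| 0.5 | 0.1500 | 0.1299 | 0.75 | 0.75 | 89.8% | 89.8% | 96.2% |
| 0.7 | 0.1162 | 0.1071 | 0.51 | 0.85 | 89.8% | 98.7% | 99.5% |

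The adjusted analysis has the highest power in every row. Which unadjusted analysis comes second depends on rho: scores at 0.3, change at 0.7.

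**Step 4: how far score and change can diverge.** The two estimated differences differ by exactly the chance difference in baseline means. Its standard error is 0.15 × √(2/48) = 0.031, so its 95% range is ±1.96 × 0.031 = ±0.06, against a target of 0.10. Of a baseline difference D, the score comparison carries rho × D and the change comparison carries −(1 − rho) × D. At rho 0.5 and D = 0.06 these are +0.03 and −0.03. Adjustment removes both.

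**The case against.** Several stronger readings are tempting, but the article does not support them.

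- **Three rival tests.** The repeated-measures ANOVA is described for variation over time, and no contrast between the arms is stated for it. The t and Wilcoxon tests are alternatives to each other. What remains is two unranked procedures, one of which branches.
- **A false-positive rate near 10%.** In simulated trials with no true effect (normal data, one visit, 48 per arm), at least one of a follow-up-score t test, a change t test and a change Wilcoxon test was significant in 9.4% to 10.3%. That counts t and Wilcoxon together and leaves the score-or-change choice open. It fits neither the ANOVA nor the growth model, so it is not this plan's error rate.
- **Power falls to 78% because baseline is left out.** The 78.0% belongs to change scores at rho 0.3, and the two procedures are worded for scores. Against scores at that rho the gain is 89.8% to 92.3%. The shortfall for change at low rho comes from using the SD of the index for a change endpoint, which is a separate sample-size question.
- **The growth curve would miss an early effect.** The text does not say that time is linear. If true differences of 0, 0.10, 0.05 and 0 at 0, 1, 6 and 12 months are fitted by a straight line, the 1-month value is 0.050 with month 0 included and 0.098 with follow-up visits only. The first-month differences that the article cites are for TAVI against full sternotomy, so they do not show when a ministernotomy benefit is expected.
- **The normality check will usually lead to Wilcoxon.** That depends on the share of patients at the ceiling, which the article does not give, and on whether scores or changes are tested.

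Two further defences have weight. The growth model already supplies mean differences with CIs and uses all available data under missing at random, so a Wilcoxon branch or an ANOVA restricted to complete cases would not leave the trial without an estimate. Baseline may also enter that model as one of the repeated outcomes, which would bring it closer to the change endpoint. The text does not settle this, and a freely estimated treatment difference at baseline is still not adjustment for it. Neither defence says which analysis is primary.

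**Conclusion.** The point holds in limited form. The article sets out two analyses for the same between-arm EQ-5D contrast, ranks neither, words both for scores although the endpoint is change, and publishes a covariate list without the baseline index.

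The gain from adjustment is certain in direction for any rho strictly between 0 and 1, but its size depends on a correlation that the article does not give. Over rho 0.3 to 0.7 the variance is 9% to 49% lower than for follow-up scores and 35% to 15% lower than for change scores. The power gain is 2.5 to 9.7 percentage points over scores and 14.3 to 0.8 points over change. These figures assume equal SDs of 0.15, normal data, a single visit and 48 evaluable patients per arm.

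The stated sample size is arithmetically correct on its own inputs. The defect is a correctable weakness in the analysis wording and does not invalidate the design.

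**What to change.** Name the longitudinal model as the single primary analysis of the EQ-5D index. Add the baseline EQ-5D index as a covariate to age, sex and EuroScore, enter follow-up visit as a category, and include treatment by visit. Report the mean difference with its 95% CI at 1, 6 and 12 months. State whether score or change is modelled. With baseline as a covariate (allowed a separate effect at each visit), the treatment estimate at a visit is the same either way.

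Do not let a normality pretest choose the primary test. Label the t/Wilcoxon tests and the repeated-measures ANOVA as supportive.

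This does not settle which of the three visits decides the trial. That needs its own rule: either one primary visit or a multiplicity adjustment over the three.

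The cost is revised wording and one model that the planned software can fit, with no new data and no extra patients. The change should be fixed before outcomes are compared by arm, through the review-board and registry route that the article describes for amendments.
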